### Participant retention

The face-to-face clinic visits are in line with routine clinical care in the study centre and would be considered clinically necessary so that patients who do not attend appointments will be called by a member of the research team and offered a further appointment. Participants who have not returned the postal questionnaires at 26 and 52 weeks will be contacted by telephone by a member of the research team.

## Data management

### Statistical analysis plan

Where variables are continuous, descriptive statistics will be presented and this will provide number of observations, number of missing observations, mean (SD), median (IQR), maximum, and minimum values. Where variables are categorical, we will present the number and % of each treatment arm.

Comparison of PWRE at 12 months (primary outcome) between treatment arms will be analyzed using a paired *t*-test. Descriptive analysis of measures at each timepoint will be presented split by treatment arm, and comparisons will be made in a similar way to the primary outcome. Grip strength and ROM at 12 weeks will be corrected using the non-affected side, and then comparison of the corrected values will be made between treatment arms using a paired *t*-test.

The comparison of complication rate and radiological success will be made between treatment arms using a binomial test for the comparison of proportions, and we will present the difference in percentage between groups accompanied by the 95% CI for the difference and p-value associated with the comparison.

For time to return to work and sports, we will analyze this using a Kaplan-Meier survival curve and present this along with the log-rank statistic comparing the two treatment arms. We will also present a breakdown of the number of dropouts by treatment arm and, if appropriate, compare this rate using a binomial test for the comparison of proportions.

The sample size calculation accounts for a 20% loss to follow-up rate. Analysis will be on an intention-to-treat basis. Per protocol and as treated analyses will also be undertaken for the primary outcome only.

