## Methods

### Trial design

A single-centre prospective randomized RCT with parallel groups allocated in a 1:1 ratio will be undertaken. The trial was registered with the International Standard Randomized Controlled Trial Number Registry (ISRCTN) as ISRCTN95922938 on 3 December 2021.

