### Sample size

A total sample size of 142 subjects (71 in each group) is required to detect a difference in mean PWRE scores between groups of 11, assuming a common standard deviation of 20 using a two-sided, two-sample test with 5% significance and 90% power.^35^ To account for a loss to follow-up rate of 20% at 52 weeks, this has been increased to 178 patients (89 per group).

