### Randomization/treatment allocation

After informed consent has been obtained and baseline information collected, participants will be randomly allocated to receive either conservative management in a cast or surgical fixation. An independent statistician generated a randomization schedule using block randomization with a random block size to allocate participants in a 1:1 ratio stratified by fracture AO/OTA classification (type A, type C) to ensure as far as possible equal numbers of each fracture type in each group. A member of staff independent of the study used this schedule to create a series of sequentially numbered opaque sealed envelopes containing the treatment allocation as specified by the statistician.

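### The primary outcome and the other continuous outcomes are to be compared between two independent randomised arms with a paired t-test, which the design cannot support and which contradicts the two-sample test used to size the trial

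*Protocol article*

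**What the plan says.** All references are to the protocol article.

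- Trial design: "A single-centre prospective randomized RCT with parallel groups allocated in a 1:1 ratio will be undertaken".
- Randomization/treatment allocation: the schedule used "block randomization with a random block size to allocate participants in a 1:1 ratio stratified by fracture AO/OTA classification (type A, type C"). Nothing here or elsewhere links a patient in one arm to a patient in the other.
- Sample size: the aim is to "detect a difference in mean PWRE scores between groups of 11", with a common SD of 20, "using a two-sided, two-sample test with 5% significance and 90% power".
- Statistical analysis plan, primary outcome: "Comparison of PWRE at 12 months (primary outcome) between treatment arms will be analyzed using a paired" t-test.
- Same section, measures at each timepoint: "comparisons will be made in a similar way to the primary outcome".
- Same section, grip strength and range of motion at 12 weeks: values are first corrected for the unaffected side, and then "comparison of the corrected values will be made between treatment arms using a paired" t-test.
- Same section, binary outcomes: "The comparison of complication rate and radiological success will be made between treatment arms using a binomial test for the comparison of proportions". Time to return to work and sports has Kaplan-Meier curves with a log-rank comparison.

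**The concern.** A paired t-test works on differences within defined pairs. It needs a one-to-one link between each observation in one group and one in the other. Here the arms hold different patients, randomised one by one. Stratifying by fracture type and blocking do not create pairs. After loss to follow-up the arms may not even have equal numbers. The named primary test therefore has no defined input.

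The team would have to invent pairs, switch to a within-patient test that does not compare the arms, or depart from the published wording. The first makes the primary p-value depend on a choice that carries no information. The second does not answer the trial question. The third is the sensible course, but it should be a recorded correction and not a silent one.

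The problem reaches the continuous secondary measures as well: PRWE at the other timepoints, QuickDASH, EQ-5D, VAS pain, grip strength and range of motion.

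**Working it through.** **Inputs from the Sample size section.** Difference 11, common SD 20, two-sided 5% level, 90% power, 20% loss at 52 weeks, 142 patients (71 per group) before loss and 178 (89 per group) after.

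**1. Reproduce the plan's figure with an independent two-sample t-test.** The standardised difference is 11/20 = 0.55. The noncentral t calculation gives 70.44 per arm, rounded up to 71, so 142 in total. Power at 71 per arm is 90.2%. For loss, 142/(1 − 0.20) = 177.5, so 178; and 71/0.80 = 88.75, so 89 per arm. The stated figures are exactly those of an independent-samples test.

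**2. What a paired calculation would need.** The SD of a within-pair difference is 20 × √(2(1 − ρ)), where ρ is the within-pair correlation. The document gives no ρ. Over an assumed range, 90% power needs:

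| ρ (assumed) | SD of differences | Pairs needed |
|---|---|---|
| 0 | 28.3 | 72 (71.4) |
| 0.3 | 23.7 | 51 |
| 0.5 | 20.0 | 37 |
| 0.7 | 15.5 | 23 |

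Only ρ = 0, where pairing serves no purpose, comes near 71. So the sample size was not derived for a paired analysis with useful correlation.

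**3. Power if pairs were invented, with ρ = 0.** Both cases below are assumptions; the document describes neither.

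- *Completers paired after follow-up.* With 71 pairs and SD of differences 28.3, power is 89.8%, against 90.2% for the independent test.
- *Pairs fixed by enrolment order, each member lost independently at 20%.* Both members are seen with probability 0.8 × 0.8 = 0.64. The expected number of complete pairs is 89 × 0.64 = 57. The SD of that count is √(89 × 0.64 × 0.36) = 4.5, so the 95% range is 48 to 66. Power is 82.3% at 57 pairs, 75% at 48 and 88% at 66. About 178 × 0.8 = 142 patients are observed and 2 × 57 = 114 are used, so about 28 are discarded.

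**4. What arbitrary pairing does to the result.** In 20,000 simulated trials with 71 per arm, power was 90.0% paired and 90.4% independent, and type I error was about 5.2% for both. Average performance is hardly changed. The single result is: in one simulated data set the independent test gave p = 0.0007, while 5,000 arbitrary pairings of the same data gave p from 0.00003 to 0.0057. All of these lie below 0.05, so in this example the conclusion at the 5% level does not change, but the p-value varies by a factor of about 200 (0.0057/0.00003 = 190).

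**5. Can another reading make the test work?** A before/after test is within patients, while the text says the comparison is between arms. An injured-against-uninjured reading fails for PRWE, since no contralateral score is described. It also fails for grip and range of motion, since the side correction is already done when the paired test between arms is applied.

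**The case against.** The strongest reply is that this is a typing slip for unpaired. The Sample size section already names a two-sample test, and each affected comparison is stated as being between arms. That is plausible, and it gives a prespecified basis for the correction. It means a reader should not infer that any remedy must be chosen after the results are known. The documents do not show that outcomes have been analysed, and a separate analysis plan may exist. But the paired test appears twice, and the first instance is carried to other measures by reference, so the text still fixes the wrong primary test.

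A reader might also infer that the trial loses its 90% power. The document does not support that. The 82% figure needs pairs fixed before follow-up and every half-observed pair dropped, which is stated nowhere. Pairing completers keeps about 90%. Nor does arbitrary pairing inflate type I error, so it would be too strong to say that every invented pairing gives an invalid test.

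Finally, a reader might take all secondary outcomes to be affected. Complications, radiological success and time to return to work and sports have their own between-arm methods, so they are outside this point.

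An article may leave analysis detail to a fuller plan, but here it names a specific test that conflicts with its own design. That is a misstatement and not an omission.

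**Conclusion.** The primary analysis is wrong as written and must be corrected. The paired test cannot be applied to independent, individually randomised arms with no defined pairs, and it contradicts the test behind the sample size. The same holds for the continuous secondary outcomes only.

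The defect is a mis-specified test, not an undersized trial. If pairs were invented, the primary p-value would depend on the pairing. Power would be 89.8% for 71 paired completers per arm, or about 82% (75% to 88%) with pairs fixed by enrolment order. Both figures assume difference 11, SD 20 and zero within-pair correlation; the second also assumes independent 20% loss in each member.

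**What to change.** In both places in the Statistical analysis plan section, replace the paired t-test with an independent two-sample t-test, which matches the Sample size section. A linear model with treatment arm and AO/OTA stratum as factors is an acceptable alternative; it goes beyond what consistency requires, but it respects the stratified randomisation. State that the chosen method applies to PRWE at 52 weeks and to all continuous secondary outcomes, including side-corrected grip strength and range of motion.

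The cost is a wording amendment, best dated before outcome data are analysed. The sample size (142, or 178 after 20% loss), data collection and trial conduct do not change.

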### Secondary outcome measures

The secondary outcome measures are detailed below:

Abbreviated version of the Disabilities of Arm, Shoulder and Hand (QuickDASH) questionnaire:^26^ an 11-question upper-limb-specific validated measure of disability with the outcome score ranging from 0 (no disability) to 100 (maximum disability), with optional work and sport/musical instrument modules.^27^EuroQol five-dimension three-level questionnaire (EQ-5D-3L): to measure health-related quality of life (HRQoL).Visual analogue scale (VAS) pain score (visual scale 1 to 10): to measure participant’s pain.Complications: occurrence will be determined at each assessment point and include complex regional pain syndrome (CRPS), diagnosed using the Budapest Criteria,^28,29^ nerve injury, tendon injury, infection, and reoperation rates.Grip strength: measured with a dynamometer and compared with the uninjured side and adjusted for hand dominance.ROM at the wrist: measured using a standard full-circle goniometer. Flexion, extension, supination, and pronation will be measured and compared with the uninjured side.Radiological assessment: pre- and post-intervention standard posteroanterior and lateral radiographs of the wrist will be used. Radial inclination, radial height, ulnar variance, palmar tilt, intra-articular gap, and intra-articular step will be measured. The presence or absence of carpal malalignment, volar hook,^30^ dorsal comminution, and volar comminution will be assessed in addition to the AO/Orthopaedic Trauma Association (AO/OTA),^31^ Zenke,^26^ and Buttazzoni classifications of the fracture.^32^ Outcome will also be assessed in detail with regards to fracture position on healing, complications, union, and the development of radiological degenerative changes.Healthcare resource use and cost-effectiveness including return to work.

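### Grip strength is defined with a hand-dominance adjustment that the stated analysis leaves out; if the side correction is a simple difference, it also gives up precision

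*Protocol article*

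**What the plan says.** Under Secondary outcome measures, the protocol article defines grip strength as "measured with a dynamometer and compared with the uninjured side and adjusted for hand dominance". For range of motion the definition is narrower: "Flexion, extension, supination, and pronation will be measured and compared with the uninjured side". Dominance is named for grip only.

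Under Statistical analysis plan, one sentence covers both outcomes: "Grip strength and ROM at 12 weeks will be corrected using the non-affected side, and then comparison of the corrected values will be made" between the arms with a paired t-test. The section mentions neither dominance nor any covariate, and does not say whether the correction is a difference or a ratio.

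Under Randomization/treatment allocation, the schedule is "stratified by fracture AO/OTA classification (type A, type C"). No other stratification factor is named, so the design does not balance dominance.

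**The concern.** The outcome definition asks for two operations on grip strength, a side comparison and a dominance adjustment. The analysis carries out only the first. Correcting by the other hand does not remove dominance. It leaves a dominance effect in the corrected value, with a sign that depends on which hand was broken.

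Grip and ROM are performance measures taken by a blinded assistant, whereas the PRWE and the other scores are answered by patients who know their treatment. They are therefore a useful check on the primary result, and avoidable noise in them matters. With the form of correction left open, two analysts could also follow the same sentence and obtain different results.

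**Working it through.** **The plan's own figure.** The article gives no SD, correlation or effect for grip or ROM. Its only calculation is for the PRWE. A difference of 11, SD 20, two-sided 5% and 90% power give 70.4 per arm by the two-sample t-test, so 71; and 71/0.80 = 88.75, so 89. Both agree with the article, but neither bears on grip.

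**What dominance does to a corrected value.** Assume the dominant hand is 10% stronger and the injured hand has recovered 60% of its own strength. As a ratio to the other hand, this reads 0.60 × 1.10 = 66% if the dominant hand was broken, and 0.60/1.10 = 54.5% if it was not. The same recovery differs by 11.5 points.

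**Side difference against covariate.** Let k be the injured/uninjured SD ratio and r the between-side correlation, with variances in units of the uninjured-side variance.

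- Difference score: k² + 1 − 2rk
- Residual after regression on the uninjured side: k²(1 − r²)
- The first minus the second: (1 − rk)², which is never negative and is zero when rk = 1

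For k = 1 the ratio of the second to the first is (1 − r²)/(2(1 − r)) = (1+r)/2.

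| r | k = 0.7 | k = 1.0 | k = 1.3 |
|---|---|---|---|
| 0.3 | 0.417 | 0.650 | 0.805 |
| 0.5 | 0.465 | 0.750 | 0.912 |
| 0.7 | 0.490 | 0.850 | 0.991 |
| 0.8 | 0.477 | 0.900 | 0.997 |
| 0.9 | 0.405 | 0.950 | 0.917 |

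Example, k = 1.3 and r = 0.8: 1.69 × 0.36 = 0.608 against 1.69 + 1 − 2.08 = 0.610, ratio 0.997. For k = 1, the equivalent increase in sample size is 2/(1+r) − 1: 54% at r = 0.3, 33% at 0.5, 18% at 0.7, 11% at 0.8 and 5% at 0.9.

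**Ratio against covariate.** The algebra above does not apply to a ratio, so this was simulated with 71 per arm and 4,000 replicates. All inputs are assumptions: strength with mean 22 and SD 6, recovery of 60% against 68%, a 10% dominance effect, and the dominant hand broken in half the patients. Recovery is proportional to the hand's own strength, with SD 0.25, 0.17 or 0.10. Power at two-sided 5%:

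| Analysis | r about 0.52 | 0.65 | 0.79 |
|---|---|---|---|
| t-test, side difference | 0.38 | 0.60 | 0.82 |
| t-test, ratio | 0.46 | 0.75 | 0.98 |
| t-test, ratio corrected for dominance | 0.48 | 0.79 | 1.00 |
| linear model, uninjured side | 0.43 | 0.72 | 0.98 |
| linear model, uninjured side and dominance | 0.45 | 0.76 | 0.99 |

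The side difference is worst throughout. The plain ratio does about as well as the covariate model, or slightly better. Adding dominance to the linear model raises power by 1.6, 4.0 and 1.4 percentage points (0.430 to 0.446, 0.719 to 0.759, 0.978 to 0.992). Two features favour the ratio: recovery is proportional by construction, and the dominance-corrected ratio uses the true 10%.

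**The case against.** The strongest reply is that the two sections are compatible. The outcome list defines the variable and the analysis section names a test on corrected values. Dominance can be built into the corrected value before any t-test is run, and in the simulation that did best. A condensed article may leave such a derivation to the full protocol or SAP.

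Part of this stands. A reader might infer that a t-test cannot accommodate dominance; the documents do not support that. They support only that the correction, as described, uses the other side and nothing else. The article chose to state both the definition and the analysis, and the second leaves out part of the first.

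Three other stronger readings also fail:

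- A reader might infer that the planned analysis is less precise in general. That is shown for a difference score only. The form is not stated, and a ratio showed no loss against the covariate model in the simulation.
- A reader might infer that the treatment comparison is biased. Allocation is randomized, so omitting dominance costs precision and leaves chance imbalance uncorrected, but does not bias the comparison.
- A reader might infer that ROM breaks the same promise. It does not, because no dominance adjustment is promised for ROM.

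It is also fair to say that choosing a covariate model over a side-corrected t-test is a matter of efficiency. The mismatch over dominance is the firmer part of the point.

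**Conclusion.** The point holds in a limited form. The article promises a dominance adjustment for grip strength, and its stated analysis contains none; nor does that analysis use the AO/OTA stratification factor. The precision argument is conditional. For a side difference with equal SDs the covariate analysis has 0.65 to 0.95 of the variance for r from 0.3 to 0.9. Over the other SD ratios tried, the figure runs from about 0.41 to 1.00. For a ratio no gain is guaranteed. All of these rest on assumed SDs and correlations, and the article gives nothing from which to size the gain from AO/OTA type. The outcomes are secondary and measured at 12 weeks, and the primary PRWE comparison is not touched by this point. The change is worth making because it costs almost nothing.

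**What to change.** - **Grip strength.** Analyse the 12-week injured-side value in a linear model with treatment arm, uninjured-side grip, whether the injured side is dominant (yes/no), and AO/OTA type. Report the adjusted mean difference with its 95% CI.
- **ROM.** Analyse each direction in the same way with arm, uninjured-side value and AO/OTA type. Dominance is not needed to honour the definition.
- **Display.** Keep percent-of-uninjured-side as a descriptive summary.
- **If a corrected value is preferred for grip.** State whether it is a difference or a ratio, state how dominance enters it, and compare the arms as independent groups.

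The linear model also removes the word 'paired' from this comparison. The design has independent parallel arms with no pairs, which is a separate defect of the same sentence.

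The cost is wording in the analysis plan, fixed before the data are seen. Uninjured-side values and AO/OTA type are already collected, and dominance must be recorded anyway to meet the outcome definition. If the uninjured side is measured after randomization, the model assumes that treatment does not affect that hand; the planned correction already makes the same assumption.

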### Eligibility criteria

The eligibility criteria are detailed in Table II. Patients must fulfil all eligibility criteria, and this will be assessed by a member of the research team prior to approaching patients to consider participation in the study. It is commonplace in the study centre for patients presenting with a displaced distal radius fracture to undergo closed reduction under Bier’s block in the emergency department (ED). However, if a patient with a displaced fracture has not undergone a Bier’s block in the ED, they would still be eligible for the trial if they meet the necessary criteria.

**Table II. T2:** Study inclusion and exclusion criteria.

**Inclusion criteria** Aged ≥ 65 years Dorsally angulated fracture of the distal radius The treating surgeon believes the patient is suitable for surgical fixation Operation date within three weeks of fracture Closed or Gustilo-Anderson grade I injury
**Exclusion criteria** Patients unable to give informed consent Patients medically unfit to undergo surgery Volar displaced fractures Partial articular and isolated radial styloid fractures Associated fractures to the upper limb and/or pre-existing pathology adversely affecting function Associated ligamentous injury, dislocation, or subluxation of the wrist Open fractures of Gustilo-Anderson grade II or higher Persisting neurovascular deficit requiring operative intervention Off-ended/severely displaced fractures post attempted reduction that are deemed to required surgery by the treating surgeon Patients who are non-resident locally and will be unable to attend for local follow-up Patients unable to comply with follow-up, including English-language patient-reported outcome measures, either on the telephone or by post

A displaced fracture will be defined as one or more of:^25^

Carpal malalignment (defined as the displacement on a lateral view of the longitudinal axis of the capitate dorsal to the longitudinal axis of the radius).Dorsal angulation of greater than 10° from the anatomical position.Radial shortening of more than 2 mm.Intra-articular step of more than 2 mm.Intra-articular gap of more than 5 mm.

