## Outcome measures

### Primary outcome measure

The primary outcome measure is the PRWE at 52 weeks post intervention.^24^ The PRWE assesses wrist function using 15 questions (rated 0 to 10) based on the patient’s pain (five questions) and disability (ten questions) to produce a score from 0 (no disability) to 100 (maximum disability).

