### Blinding

Due to the obvious differences between the two interventions, patients will not be blinded, nor will those who undertake radiological analysis. A blinded research assistant will undertake grip strength and ROM assessment at weeks six and 12.

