The trial has some potential limitations. Closed reduction under Bier’s block in the ED forms a routine part of the management pathway for dorsally displaced fractures of the distal radius in the study institution. Patients are then followed up in the fracture clinic to assess for re-displacement. The authors are aware that many centres do not employ such a protocol and therefore closed reductions are carried out in the theatre setting. There could thus be a temptation to utilize K-wires to maintain this reduction while patients are already in theatre, despite recent evidence to the contrary in the form of the DRAFFT-2 trial.^40^ Nevertheless, this could potentially limit the generalizability of conclusions. ORIF using volar plate fixation forms the mainstay of operative intervention in the study centre, although there is variation and in some centres K-wires are commonly used for fractures that are reducible closed. Although the method of fixation may vary, the key question to address here is whether the resulting pain and functional outcome of elderly patients can be improved by achieving a more anatomical radiological fracture position. Despite being one of the most commonly used joint-specific patient-reported outcome measures used in the assessment of pain and function following fracture of the distal radius, the PRWE is known to have a ceiling effect.^41,42^ However, in the current literature there is no superior patient-reported outcome measure.

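### The per-protocol and as-treated analyses of 52-week PRWE are open to selection bias; a complier-average estimate that uses the randomisation is a cheap addition

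*Protocol article*

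**What the plan says.** The Statistical analysis plan section of the protocol article sets the main basis: "Analysis will be on an intention-to-treat basis". It then adds two further analyses: "Per protocol and as treated analyses will also be undertaken for the primary outcome only". The article does not say what these two are meant to show.

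Three other places bear on whether treatment received may differ from allocation:
- Table II (Eligibility criteria) requires of every participant, in both arms: "The treating surgeon believes the patient is suitable for surgical fixation".
- The Blinding section says "patients will not be blinded, nor will those who undertake radiological analysis".
- The Discussion describes the centre's routine pathway after closed reduction: "Patients are then followed up in the fracture clinic to assess for re-displacement".

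The article gives no rate, timing, reason or rule for a cast patient to have surgery later, or for a surgery-arm patient to go without it.

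**The concern.** A per-protocol analysis removes patients who departed from their allocation. An as-treated analysis moves them to the other group. In either case the groups being compared are no longer those that randomisation formed.

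If departures are related to prognosis, the difference between the groups mixes the effect of the operation with the difference in prognosis. In this trial a plausible route is a cast patient who was suitable for fixation from the start, knows the allocation, is seen in clinic with poor position or progress, and then has surgery. Per-protocol would take that patient's poor outlook out of the cast arm. As-treated would also add it to the surgery group.

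At stake is the interpretation of the result. If cross-over is appreciable, the intention-to-treat difference is diluted, and readers will turn to the other two estimates for the effect of having the operation. Those estimates can be further from that effect than the diluted one.

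**Working it through.** **The plan's own figure.** The Sample size section assumes a difference of 11 and SD 20 ("is required to detect a difference in mean PWRE scores between groups of 11, assuming a common standard deviation of 20"), at a two-sided 5% level with power of 90%.
- Normal approximation: n per arm = 2 × (1.960 + 1.282)² × 20² / 11² = 69.5, so 70.
- Two-sample t version: 70.44, so 71 per arm and 142 in total.
- With 20% loss: 142 / 0.8 = 177.5, so 178.

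The stated figures reproduce.

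**Inputs for the bias.** SD 20 and the 11-point difference come from the article. PRWE runs from 0 to 100 and higher is worse. The cross-over share c and the correlation r between the latent reason for cross-over and the 52-week PRWE without surgery are not in the article. They are assumed, with c from 5% to 20% and r from 0 to 0.5. Outcomes are treated as normal, which ignores the bounds of the scale.

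**Cast-to-surgery cross-over only, no true effect.** The patients who cross over are worse than average by

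k = r × 20 × φ(z)/c, with z the upper-c point of the standard normal and φ its density.

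For c = 10%, φ(1.2816)/0.1 = 1.755. With r = 0.5, k = 0.5 × 20 × 1.755 = 17.55.
- Per-protocol shift: c × k/(1 − c) = 1.755/0.9 = 1.95 against surgery.
- As-treated shift: c × k/(1 − c) + c × k/(1 + c) = 1.95 + 1.755/1.1 = 1.95 + 1.60 = 3.55 against surgery.

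With r = 0.3, k = 10.53 and the shifts are 1.17 and 2.13.

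| c | r | Per-protocol | As-treated |
|---|---|---|---|
| 5% | 0.3 | 0.65 | 1.24 |
| 5% | 0.5 | 1.09 | 2.07 |
| 10% | 0.3 | 1.17 | 2.13 |
| 10% | 0.5 | 1.95 | 3.55 |
| 20% | 0.3 | 2.10 | 3.50 |
| 20% | 0.5 | 3.50 | 5.83 |

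A simulation with 400,000 patients per arm agrees within 0.1 point. It gives 1.9 and 3.5 at c = 10%, r = 0.5, and intention-to-treat stays at 0. With r = 0 all shifts are zero.

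**True benefit of 11, cross-overs receiving the full benefit, c = 10%.**
- Intention-to-treat: 11 × 0.9 = 9.9.
- Per-protocol: 11 − 1.17 = 9.8 (r = 0.3) to 11 − 1.95 = 9.1 (r = 0.5).
- As-treated: 11 − 2.13 = 8.9 to 11 − 3.55 = 7.5.
- Complier-average: 9.9 / 0.9 = 11.0, the intention-to-treat difference divided by the between-arm difference in the share receiving surgery. It returns 11 because the model lets allocation act only through the operation.

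**Departures from the surgery arm.** If 10% of the surgery arm and none of the cast arm goes without the operation, and these patients have worse prognosis (r = 0.5), the same formulas change sign. Against a true 11, the simulation gives 13.0 per-protocol and 14.6 as-treated. If 10% switch in each arm with equal selection, both return 11.0.

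**Scale.** With 71 per arm the standard error of the difference is 20 × √(2/71) = 3.36. The complier-average standard error at c = 10% is about 3.36 / 0.9 = 3.73.

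**The case against.** Intention-to-treat with per-protocol and as-treated analyses beside it is conventional, and no sentence in the article is wrong. A reader might infer that the plan deals with cross-over through these two analyses. The text does not say so: they are additions, and the basis of analysis is intention-to-treat. That part of the objection stands in full.

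A reader might also infer that the cast patients who do worst will be operated on, so that the bias must run against surgery. The documents do not support this. The Discussion sentence on re-displacement describes routine care and is given as a limit on generalisability, not as a trial rule. The Introduction accepts that a fracture treated in a cast may heal displaced. Table II excludes severely displaced fractures judged to need surgery, which removes some likely cross-overs. Early displacement need not track 52-week PRWE, and departures from the surgery arm can cancel or reverse the shift.

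The size is also modest. At 10% cross-over the per-protocol shift is at most 1.95 / 3.36 = 0.6 of a standard error, and the as-treated shift about 1.1. Claims that harm would be created or benefit hidden go too far: with a true 11, even the 7.5 as-treated estimate is 7.5 / 3.36 = 2.2 standard errors from zero. On the other hand, this bias does not shrink with more patients, and in that scenario as-treated misses by 3.5 points where intention-to-treat misses by 1.1.

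Finally, the complier-average estimate has assumptions of its own, and the full protocol and analysis plan are not shown. It cannot be claimed that no other analysis of treatment received is planned. What remains is that the two estimators the article does name are open to selection.

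**Conclusion.** The point holds in a conditional form. The two added analyses of 52-week PRWE condition on events after randomisation and are open to selection bias of unknown size. If cross-over follows poor progress in cast, both move against surgery, as-treated more than per-protocol: about 2.1 to 3.5 and 1.2 to 1.9 points at an assumed 10% cross-over and correlation 0.3 to 0.5. Neither the rate nor the correlation is documented, and the direction is not fixed. If switching is unrelated to prognosis, these two analyses are unbiased and it is intention-to-treat that is diluted. Since readers could not tell which case applies, neither estimate is a sound basis for inference about receiving the operation. The primary intention-to-treat comparison is not touched by this bias. This is a cheap improvement.

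**What to change.** Keep intention-to-treat as the primary analysis. Report the number of cross-overs and the reasons, by arm and in both directions.

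Add a complier-average causal effect estimate for 52-week PRWE, by two-stage least squares, with randomised allocation as the instrument and receipt of plate fixation within a pre-stated window as treatment received. The window matters because later surgery may not have the same effect as early plating. State the assumptions: allocation affects PRWE only through treatment received, and no patient would always do the opposite of the allocation. If the per-protocol and as-treated analyses stay, label them descriptive.

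The cost is a few sentences of analysis text and one extra model. The Follow-up assessments section already has treatment and reoperations recorded at each visit. The drawbacks are a wider interval (standard error about 3.73 instead of 3.36 at 10% cross-over) and reliance on the first assumption, which is less secure in an open trial with a self-reported outcome. The change is best made before results are seen.
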